It has shown in previous studies that the effectiveness of BFR with LLRT is not conclusive compared with LLRT alone [26]. For instance, Ferraz et al. demonstrated that LLRT with BFR is more effective in relieving pain compared with LLRT alone [22], while another study suggested that there was no difference between the two approaches [19]. Therefore, in this study, we set a group of LLRT without BFR to investigate whether LLRT with lower LOP is more effective than LLRT alone. Due to the fact that health education constitutes a minimized intervention that is nonetheless important for KOA [27], we set health education as a control group for comparison with the other three groups. The aim of this study is to investigate the efficacy of LLRT with different degrees of BFR in patients with KOA. Our measures will include pain, self-reported function, physical functional performance, muscular strength, muscle thickness, and QoL. We will also observe any adverse events to verify the safety of BFR training during the study.

Hypotheses:
LLRT, LLRT with low BFR (40% LOP), and LLRT with high BFR (80% LOP) will all be more effective than health education.Both LLRT with 40% BFR and 80% BFR will be more effective than LLRT alone, but there will be no difference between the two levels of BFR.

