### Intervention

All participants in the intervention groups will complete 24 exercise sessions over 12 weeks, with two sessions per week, as described in Table 1. During the 12 weeks, the participants may continue their previous activities without aggravating their knee symptoms. In an individual exercise session, each group will perform a warm-up exercise to prevent injuries before the formal exercise protocol. Moreover, the pain intensity will be monitored using a VAS during the exercise, with some pain considered as acceptable. However, the load will be decreased by 20% if the pain intensity is higher than 20 mm/100 mm on the VAS [32]. During the period of intervention, all participants are not allowed to accept any other form of therapy, including medications.

**Table 1 Tab1:** Treatment protocol performed by the LL group and the BFR groups

LL group and BFR groups	
• Hamstrings stretching, 3 repetitions of 30 s	
• Bridge with isometric contraction of the transversus abdominis-CORE training, 3 repetitions of 30 s^+^	
• Hip abduction with weights (side lying), 3 sets of 10 repetitions^+^	
• Calm exercises (side lying) with an elastic band, 3 sets of 10 repetitions^+^	
• Calf raises with weights (standing), 3 sets of 10 repetitions^+^	
• Sensori-motor training (standing) at mini-trampoline, 3 repetitions of 30 s	
• Leg press (machine), 0–60°, 3 sets of 15 repetitions*	
• Seated knee extension (machine), 90°–0° of knee flexion, 3 sets of 15 repetitions*	

*Load is 30% of the 1-repetition maximum

^+^The load will be adjusted every 4 weeks to maintain an effort of perception between 6 and 7 on the Borg scale

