#### Blood flow restriction exercise groups

All participants from the High BFR and Low BFR groups will be individually measured for the LOP and re-evaluated every 2 weeks during the study. The LOP will be measured with the participants in relaxed and supine positions. The portable color Doppler ultrasound (LOGIQ e, General Electric Company, Boston, USA) will be positioned at the ankle to measure the pedal pulse. A pneumatic cuff (7-cm width and 56-cm length) will be placed on the proximal thigh of the participant and inflated until the pedal pulse vanishes on the Doppler ultrasound. We will then slowly deflate the cuff, and when the pedal pulse returns, we will record the LOP. The Low BFR group will perform at 40% LOP, while the High BFR group will perform at 80% LOP during the exercise. The loads for the leg press and knee extension exercises will be 30% of the 1RM (estimated by 7–10 RM). Furthermore, participants in the High BFR and Low BFR groups will perform one set of 30 repetitions (or until exhaustion) and three sets of 15 receptions with a 30-s interval between sets [20]. The LOP will be adjusted every time to maintain a similar degree of BFR for each individual.

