#### Low-load resistance exercise group

The LL group will conduct a sham BFR, in which the pneumatic cuff will be placed on the proximal thigh of the participant with adequate space for two or more fingers between the thigh and cuff. However, no pressure will be applied to the pneumatic cuff. The exercise protocol of the LL group is the same as the BFR group. The LL group will perform three sets of 15 repetitions with 30% 1RM and 30-s intervals between sets [19, 21, 32].

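### The leg press and knee extension dose is stated two ways; if the arm-specific text governs, the BFR-versus-LL contrast mixes cuff pressure with training volume

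*Protocol article*

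**What the plan says.** Three places in the protocol article point to equal doses in the exercise arms:

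- **Intervention, opening sentence:** "All participants in the intervention groups will complete 24 exercise sessions over 12 weeks, with two sessions per week, as described in Table 1".
- **Table 1:** its title is "Treatment protocol performed by the LL group and the BFR groups". For leg press and for seated knee extension it lists "3 sets of 15 repetitions", both at 30% of 1RM.
- **Low-load resistance exercise group:** "The exercise protocol of the LL group is the same as the BFR group".

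Two places point to unequal doses:

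- **Blood flow restriction exercise groups:** patients in both BFR arms "will perform one set of 30 repetitions (or until exhaustion) and three sets of 15 receptions with a 30-s interval between sets" (the word before the rest interval evidently means repetitions). This sentence names no exercise, but it directly follows "The loads for the leg press and knee extension exercises will be 30% of the 1RM".
- **Low-load resistance exercise group, after the sentence that equates the protocols:** "The LL group will perform three sets of 15 repetitions with 30% 1RM and 30-s intervals between sets".

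The Background gives the purpose of the LL arm: "we set a group of LLRT without BFR to investigate whether LLRT with lower LOP is more effective than LLRT alone". The second hypothesis predicts that both BFR arms will beat LL and will not differ from each other. The Discussion describes the exercise arms as 0%, 40% and 80% LOP.

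**The concern.** The experimental treatment is not fixed. A therapist could give a BFR patient 45 repetitions per exercise, or up to 75, and follow the text either way.

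The LL arm is there to isolate what restriction adds: it has the same relative load, and an uninflated cuff as a sham. If the arm-specific sections are what is delivered, the BFR arms also receive an additional set on both quadriceps exercises. Pressure and volume then change together between LL and BFR.

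An effect of the additional set alone would produce the pattern that the second hypothesis predicts, with both BFR arms better than LL and no difference between 40% and 80%. The trial could appear to confirm that hypothesis with no effect of restriction at all. The limitations listed in the Discussion do not mention a volume difference.

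**Working it through.** The protocol gives no total repetition count to reproduce, so the figures below follow from its stated set schemes. The 75 is a ceiling, because the first BFR set may stop at exhaustion.

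**Inputs**
- Table 1, LL and BFR alike: 3 sets of 15 on each of two exercises.
- BFR groups section: one set of 30 (or until exhaustion) plus 3 sets of 15.
- LL group section: 3 sets of 15.
- Intervention section: 24 sessions.
- I read the BFR scheme as applying to leg press and knee extension. The preceding sentence names those two at 30% of 1RM, and they are the only Table 1 exercises with that load.

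**Per exercise and session**

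| Source | Arms | Sets | Repetitions |
|---|---|---|---|
| Table 1 | LL and BFR | 3 | 3 × 15 = 45 |
| BFR groups section | 40% and 80% LOP | 1 + 3 = 4 | 30 + 3 × 15 = up to 75 |
| LL group section | LL | 3 | 3 × 15 = 45 |

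The BFR arms therefore have two stated doses, 45 and up to 75. This inconsistency is certain.

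**BFR against LL if the arm-specific sections govern**
- Sets: 4/3 = 1.33, or 33% more, whatever the length of the first set.
- Repetitions: 75/45 = 1.67, or up to 67% more.

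**Whole course** (2 exercises × 24 sessions = 48 exercise-sessions)
- Sets: 4 × 48 = 192 against 3 × 48 = 144.
- Repetitions: up to 75 × 48 = 3,600 against 45 × 48 = 2,160, a difference of up to 1,440.

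**BFR against LL if Table 1 governs:** 45 against 45, a ratio of 1.00, with no confound.

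**Contrasts affected.** Four arms give 4 × 3 / 2 = 6 pairwise contrasts.
- Two carry the confound: 40% against LL and 80% against LL.
- One does not: 40% against 80%, where the prescription is the same in both arms.
- Three are not challenged: those with health education.

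**Why analysis cannot repair it.** Every BFR patient is assigned the additional set and no LL patient is. Prescribed volume is completely aliased with restricted versus unrestricted training. The 40%-versus-80% contrast cannot settle the matter either, because no difference there is equally what an effect of volume alone would give.

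**The case against.** The strongest reply is that Table 1 is only a shared overview and that the arm-specific sections govern. Each states its own set scheme with its own citations. Calling the LL protocol the same as that of the BFR group may mean only that the exercise programme is shared; otherwise there would be little reason to restate the sets in the next sentence. This is a reasonable reading, but the document does not say so, and the reading makes the confound real: the double dose disappears and unequal volume between BFR and LL remains.

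A second reply is that the arms may be deliberate regimens taken from published schemes, and that the second hypothesis can be read as a regimen comparison. That would be a legitimate design, but the Background and the Discussion frame the contrast as one of restriction.

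A third is that prescribed volume is not delivered volume. The first set may end early, and the Intervention section cuts the load by 20% when exercise pain exceeds 20 mm. The actual ratio could therefore fall below 1.67 by an unknown amount. That stands, and it is why the repetition figures are given as ceilings. The exhaustion rule could also make completed repetitions differ between 40% and 80% LOP, but that would be a consequence of pressure rather than a confounder.

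Finally, four of the six contrasts are unaffected or unchallenged, including 40% against 80%, which motivates the trial. This limits the reach of the problem but leaves the first half of the second hypothesis exposed.

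**Conclusion.** The concern holds and must be fixed. It is certain that the protocol states two incompatible doses for the BFR arms on leg press and knee extension, and that the LL section contradicts the BFR section.

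The confound is conditional. If the arm-specific sections govern, the two BFR-versus-LL contrasts compare pressure plus an additional set with neither, and a benefit could not be attributed to restriction. If Table 1 governs, the only fault is that the BFR section misstates the treatment.

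The conclusion rests on reading the BFR set scheme as applying to the two 30% 1RM exercises. The document gives no effect of extra repetitions on pain or any other outcome, so no bias in mm or SD is claimed.

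**What to change.** State in Table 1 and in both arm-specific sections the one scheme used in each arm. Recruitment was in progress according to Trial status, but the article does not say which scheme patients have trained under, so the sponsor must first establish that.

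- **(a) If the arms train equally, or no patient has yet trained under unequal schemes:** prescribe one set-and-repetition scheme for all three cuffed arms, correct whichever text disagrees, and leave the second hypothesis as it is.
- **(b) Only if patients have already trained under unequal schemes:** keep those schemes so that doses are not mixed within arms. Correct Table 1 and delete the sentence that equates the LL and BFR protocols. Report completed repetitions and load by arm, which would also help to show any dose variation that has already occurred. Interpret BFR versus LL as a BFR regimen (pressure plus the additional set) against low-load training. The description of the arms as 0%, 40% and 80% LOP can stay with that caveat.

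The cost is a short text correction, with no extra patients or visits. Under (a) nothing is lost from the hypotheses. Under (b) the claim for BFR over LL is narrower, and repetitions and load must be reported by arm.

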#### Low-load resistance exercise group

The LL group will conduct a sham BFR, in which the pneumatic cuff will be placed on the proximal thigh of the participant with adequate space for two or more fingers between the thigh and cuff. However, no pressure will be applied to the pneumatic cuff. The exercise protocol of the LL group is the same as the BFR group. The LL group will perform three sets of 15 repetitions with 30% 1RM and 30-s intervals between sets [19, 21, 32].

#### Health education group

The individuals in the health education group will attend sessions related to protecting their knee joints during daily life. The sessions will be conducted once a week for 12 weeks. Moreover, we will introduce the basic concept of KOA and the methods used to manage the risks of KOA through various articles from the Internet and leaflets.

### Outcome measures

#### Primary outcome measure

Pain

A VAS will be used to evaluate pain intensity at rest and under maximum situations during the last week. The VAS comprises a line with a length of 100 mm, in which “0 mm” corresponds to no pain and “100 mm” to the worst pain imaginable [40]. The VAS depicts pain effectively and is easily operated and widely applied in patients with KOA. The VAS will be evaluated at baseline and 12 and 24 weeks after the randomization of the participants. Notably, the minimal clinically important improvement for pain is about 20 mm/100 mm [41].

#### Secondary outcome measures

Self-report function

The knee function self-report outcomes will be measured using the WOMAC. This is a 24-item self-report questionnaire that assesses joint pain, stiffness, and physical functions related to KOA [42]. The maximum WOMAC score is 120, where a higher score indicates worse symptoms and functions of the knee. The Chinese version of the WOMAC has been shown to be both valid and reliable, as well as sensitive to changes in patients with KOA [43]. The WOMAC will be measured at baseline and 12 and 24 weeks after the randomization of the participants.
2.Physical function performance

The physical function performance will be assessed by the timed up and go (TUG) test [44]. Previous studies have found that the TUG test has a good intra- and inter-rater reliability (0.97 and 0.96, respectively) for KOA patients with Kellgren-Lawrence grades 1–3 [45]. During the test, the subject is timed and required to independently rise from an armchair that is 45 cm in height, walk forward following a straight line for 3 m, turn, walk back, and sit again. The average of three measurements will be used for analysis. The TUG will be measured at baseline and 12 weeks after the randomization of the participants.
3.Muscle strength

The quadriceps muscle strength will be evaluated by strength test of knee extension with an isokinetic test system (IsoMed 2000, D&R Ferstl GmbH, Hemau, Germany). Before the strength test, the participants will be fastened onto a dynamometric chair in a 90° sitting position, with the torso and thighs fixed by rigid belts. Then, the axis of the dynamometer will be adjusted in alignment with the center of the knee. Furthermore, the range of motion will be set individually for the participants by asking them to extend and flex their knees to maximum ranges. They will need to perform five constant flexion and extension motions using concentric contractions without a gravity-compensation model at three angular velocities of 60°/s, 90°/s, and 120°/s [46]. During the test, the participants will be encouraged to perform at their maximum effort [47]. The data will be recorded and calculated as the peak torque in Newton-meters, peak torque/body weight, and power in watts. Previous studies have demonstrated that the test–retest reliability for an isometric knee muscle strength assessment is 0.83 in patients with KOA [48]. The quadriceps muscle strength will be measured at baseline and 12 weeks after the randomization of the participants.
4.Muscle thickness

The muscle thickness of the quadriceps will be measured using a portable color Doppler ultrasound [32, 49]. Intra-rater and inter-rater reliabilities have demonstrated good validation when evaluating the muscle by ultrasound. Furthermore, the correlations between the ultrasound and magnetic resonance imaging (MRI) scans for muscle thickness of the vastus medialis, vastus lateralis, and rectus femoris are 0.86, 0.94, and 0.86, respectively [50, 51]. During the test, the probe will be placed at the mid-belly of these three muscles without depressing the skin. Each muscle will be measured from the adipose tissue–muscle interface to the muscle–bone interface three times. The images will be saved and then averaged. The size of the quadriceps will be estimated as the sum of these three muscles. The muscle thickness will be measured at baseline and 12 weeks after the randomization of the participants.
5.Quality of life

The 36-item Short Form Health Survey (SF-36) is a brief self-report questionnaire with 36 questions relevant to QoL in eight health dimensions, including emotional aspects, physical aspects, social aspects, vitality, bodily pain, general health, physical functioning, and mental health in psychometric properties. It can be summarized in two health scores, namely, physical and mental components, where higher scores indicate a better health condition. Previous studies have indicated that the Chinese version of the SF-36 is a relative and valid questionnaire for the general population. The SF-36 will be measured at baseline and 12 weeks after the randomization of the participants.
6.Adverse events

All adverse events will be recorded throughout the entirety of the trial. Patients will be made aware of potential adverse events during the consent process and instructed to notify a researcher when adverse events occur. Accidental injuries will be collected through systematic participant spontaneous reporting. Potential adverse events of BFR or RT include muscle soreness, knee pain, subcutaneous hemorrhage, and numbness. Additionally, physiotherapists and related specialists will categorize adverse events as treatment-related or not and monitor the severity of the adverse events within 24 h. We will report all adverse events and describe whether they are related to the study.

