**Methods:**

This is a study protocol for a randomized, controlled trial with blinded participants. One hundred individuals will be indiscriminately assigned into the following groups: two training groups with a BFR at 40% and 80% limb occlusion pressure (LOP), a training group without BFR, and a health education group. The three intervention groups will perform strength training for the quadriceps muscles twice a week for 12 weeks, while the health education group will attend sessions once a week for 12 weeks. The primary outcome is pain. The secondary outcomes include self-reported function, physical function performance, muscle strength of the knee extensors, muscle mass of the quadriceps, quality of life, and adverse events. Intention-to-treat analysis will be conducted for individuals who withdraw during the trial.

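### Adverse events rest on participant notification, with 24 scheduled contacts in the exercise arms and 12 under health education, so that safety comparison is open to unequal ascertainment

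*Protocol article*

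**What the plan says.** The abstract of the protocol article ends its list of secondary outcomes with "muscle mass of the quadriceps, quality of life, and adverse events". The adverse-events item under Secondary outcome measures sets the scope: "All adverse events will be recorded throughout the entirety of the trial".

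The same item gives the route by which events arrive. Participants are told about possible events at consent and are "instructed to notify a researcher when adverse events occur". A separate sentence deals with injuries: "Accidental injuries will be collected through systematic participant spontaneous reporting". The expected events are all effects of the exercise interventions: "Potential adverse events of BFR or RT include muscle soreness, knee pain, subcutaneous hemorrhage, and numbness".

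Scheduled contact differs by arm. The Intervention section gives the three exercise groups "24 exercise sessions over 12 weeks, with two sessions per week" and has pain monitored by VAS during exercise. For health education, "The sessions will be conducted once a week for 12 weeks", and no comparable monitoring is described.

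The Background says that events are observed in order to verify the safety of BFR training. The Discussion says that short-term safety will be examined across all four groups.

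**The concern.** Two features of the stated method matter.

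First, the injury sentence contradicts itself. Systematic collection means that staff ask everyone in the same way; spontaneous collection means that participants volunteer. A reader cannot tell which was intended. The rule for adverse events in general, that the participant notifies a researcher, is of the volunteered kind.

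Second, when events are volunteered, the number recorded can depend on how often participants meet someone to tell. The exercise arms have twice as many scheduled meetings as health education. They are also asked about pain during exercise, and knee pain is one of the four listed events. With the same true event rate, the exercise arms could show more events simply because there were more occasions to mention them.

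A separate effect acts in all arms. Mild, short-lived events such as numbness or subcutaneous hemorrhage, for which no active check is described, may go unmentioned, so absolute counts may be too low everywhere.

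At stake is the four-group reading of safety. The Data management section also makes adverse events the sole basis on which the monitoring board may close the trial early, so completeness of the count matters beyond the final report.

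**Working it through.** **Inputs from the article.** Exercise arms: 2 sessions per week × 12 weeks = 24. Health education: 1 × 12 = 12. The article gives no adverse-event rate, no reporting probability and no planned adverse-event test, so it has no figure of its own to reproduce here.

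**Assumptions.** The true event rate is the same in every arm. An event is mentioned at any one contact with probability p, independently between contacts, with p from 0.2 to 0.5. It remains reportable for a window of w weeks, and only at scheduled sessions.

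**Formula.** An event is captured with probability 1 − (1 − p)^c, where c is the number of contacts in the window: c = 2w in the exercise arms and c = w in health education. The apparent ratio is

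[1 − (1 − p)^(2w)] / [1 − (1 − p)^w] = 1 + (1 − p)^w.

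Under this model it always lies between 1 and 2.

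| Window | Contacts, exercise v health education | Ratio at p = 0.2 | Ratio at p = 0.5 |
|---|---|---|---|
| 1 week | 2 v 1 | 0.36 / 0.20 = 1.80 | 0.75 / 0.50 = 1.50 |
| 2 weeks | 4 v 2 | 1 + 0.8² = 1.64 | 1 + 0.5² = 1.25 |
| 4 weeks | 8 v 4 | 1 + 0.8⁴ = 1.41 | 1 + 0.5⁴ = 1.06 |
| 12 weeks | 24 v 12 | 1 + 0.8¹² = 1.07 | 1 + 0.5¹² = 1.00 |

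**If participants notify when the event occurs**, as they are instructed to do, the number of sessions is irrelevant and the ratio is 1.0.

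**Sensitivity to p.** Below the assumed range, even the full 12-week window leaves a visible ratio: 1.28 at p = 0.10, 1.54 at p = 0.05 and 1.78 at p = 0.02.

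**Absolute capture.** In the one-week case the exercise arms record 36% to 75% of events and health education 20% to 50%. The shortfall is therefore 25% to 64% in the exercise arms and 50% to 80% in health education. Every arm loses events; the arms differ in how many.

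**Among the exercise arms.** High BFR, Low BFR and LL each have 24 sessions, so the ratio between any two of them is 1.00 for every p and w.

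**The case against.** The strongest reply is that the instruction to notify a researcher is the same in every arm and is tied to the event, not to attending a session. If participants follow it, unequal session counts do no harm. This stands: unequal ascertainment is a risk, not an established fact, and the lower end of the range is 1.0.

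It is also fair that the injury sentence covers accidental injuries only, so it cannot be read as the collection rule for all adverse events. The general rule is nevertheless participant-initiated too.

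A journal article may leave the enquiry form to the full protocol or manual, and the absence of a form is not the point here. The point rests on what the article states: a volunteered route, and a description of injury collection that contradicts itself. Likewise, the lack of any described session between weeks 12 and 24 is only silence, since recording covers the whole trial and a week-24 assessment is scheduled.

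A reader might infer that BFR would look falsely safe. The documents do not support that. Extra contact raises the exercise-arm counts relative to health education, which would make BFR look worse. Low overall capture is a different effect, and it acts in every arm. Nor is under-counting specific to BFR shown: those participants are told of possible events at consent, are seen twice a week and have pain monitored during exercise.

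Finally, the adverse-events item promises reporting and a judgement of relatedness, not a formal test against health education. That limits the consequence but does not remove it, because the Discussion still promises a four-group look at safety.

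**Conclusion.** The point holds in limited form. The wording on injuries must be reconciled, and the comparison of the exercise arms with health education is open to unequal ascertainment in the direction of more recorded events under exercise. Volunteered reporting may also lower counts of mild events in all arms.

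The size is not determined by the article. For p of 0.2 to 0.5 and equal true rates, the apparent ratio lies between about 1.0 and 1.8. The upper end needs p = 0.2, a one-week window and reporting only at sessions. It should not be quoted as the expected bias.

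Two stronger readings should be avoided. One is that the comparison is certainly biased; the article gives no reporting probability and does not tie notification to attendance. The other is that the whole safety assessment is compromised; contact frequency does not touch the contrasts among High BFR, Low BFR and LL, which bear most directly on the safety of restriction. The primary analysis and the sample size are unaffected.

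**What to change.** 1. Reword the injury sentence to say whether collection is solicited, volunteered or both.
2. Add one short fixed enquiry: the four listed events plus one open question. Ask about knee pain as new or worse than usual. Participants are enrolled with average pain of at least 40 on the 100-mm scale, so a plain knee-pain item would largely count the disease and overlap with the primary outcome.
3. Ask it in identical words once a week in all four arms, at one of the two exercise sessions or at the education session, and again at the week-12 and week-24 assessments.
4. Use the solicited events for between-arm comparison and list volunteered events separately.
5. Recruitment was already under way according to Trial status, so report events collected before and after the change separately. For the earlier period, state that the health-education comparison is subject to unequal ascertainment.

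**Cost.** One form and about a minute at each existing contact: 12 weekly contacts + 2 assessments = 14, or roughly 14 minutes per participant. Absolute counts of mild events will rise in every arm, and a mid-trial start leaves two collection periods that cannot simply be pooled.
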